## Discussion

PPI has a significant impact on the QoL of patients who underwent radical prostatectomy. It is closely associated with the trauma caused by surgery [27, 28]. Although urinary incontinence after prostate cancer heals within half a year, the need for active improvement of symptoms and the QoL of patients is widely recognized [29]. Surgical resection of prostate cancer mainly includes bladder neck, bilateral vas deferens ampulla, bilateral seminal vesicles, and the intact prostate. Although a complete resection of the tumor and avoidance of positive surgical edge can be achieved, the bladder neck and part of the prostatic apex urethra are always removed, which will lead to the urinary control structure damage. In addition, due to destructive surgical operate, intraoperative bleeding, tumor infiltration, and tissue adhesion, the distal sphincter, fascia, ligament, and pelvic floor muscles may be damaged, which leads to postoperative urinary incontinence [30, 31]. The efficacy of acupuncture has been proved by many RCTs [32]. A systematic review demonstrated that acupuncture was an appropriate adjunctive therapy for PPI, but the supporting evidence was insufficient. These limitations included small sample size, greater-than-anticipated withdrawal, the lack of a control group, and unclear statements about randomized allocation. Therefore, much stronger evidence is still needed to verify the efficacy and safety of acupuncture for PPI. We have presented the design of this RCT mainly focuses on the therapeutic effects of verum acupuncture compared with sham acupuncture on PPI. Completion of this trial will contribute to verifying the efficacy of acupuncture for the treatment of PPI. This multicenter study covers 13 provinces and cities from south to north of China. We hope that the results will provide robust evidence to support the application of acupuncture in the treatment of postoperative incontinence of prostate cancer.

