**Methods:**

Twenty hospitals will recruit 340 participants with urinary incontinence after radical prostatectomy in China from April 2021 to April 2022. Participants will be randomly allocated to acupuncture or sham acupuncture with a 1:1 ratio using computerized simple random sampling. The study plan consists of 1-week baseline, 6-week treatment, and 18-week follow-up. Eighteen 30-min sessions of acupuncture or sham acupuncture treatment will be provided between weeks 1 and 6. The primary outcome is the change in the International Consultation on Incontinence Questionnaire-Urinary Incontinence Short Form (ICIQ-UI-SF) score at the week 6 from the baseline. Secondary outcomes include the change in volume of urine leakage at weeks 4 and 6 from a baseline measured using the 1-h pad test; 72-h incontinence episode frequency based on a 72-h voiding diary; change in the Expanded prostate cancer Index Composite scale (EPIC-26); change in the Self-Rating Anxiety Scale; weekly consumption of pads; and the severity of urinary incontinence based on a 72-h bladder diary and self-assessment of the therapeutic effect. The safety of acupuncture will also be assessed.

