#### Inclusion criteria

Patients who meet all the following requirements will be allowed to enroll:
Patients who have received radical prostatectomy with a definite pathological diagnosis of prostate cancer:Patients with urinary incontinence symptoms, which refer to the meaning of urinary incontinence by the International Continuity Society or evaluated by the urologists as experiencing urinary incontinence resulting from radical prostatectomy [23];Karnofsky Score ≥ 60 or Eastern Cooperative Oncology Group (ECOG) Score 0–2; andWilling to participate in the study and sign the consent forms.

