#### Exclusion criteria

Patients who meet all the following criteria will be excluded:
Urgency urinary incontinence caused by detrusor overactivity and bladder spasm, and urinary incontinence caused by neurogenic urethral dysfunction;Urinary incontinence treated by cystostomy, urethral sphincter reconstruction, or urethral suspension;Currently receiving less than 6 months treatment similar to acupuncture (such as electroacupuncture, warm moxibustion, and warm acupuncture);Judged by urologists as complete urinary incontinence;Urinary tract infection (except asymptomatic bacteriuria);History of severe arrhythmia, severe cardiac insufficiency, acute myocarditis, constrictive pericarditis, pericardial tamponade, severe valvular disease, heart failure, or other serious heart diseases;History of severe liver injury or potentially severe liver disease (ALT or AST > 10 times normal);History of severe renal impairment (estimated GFR < 25 mL/min/1.73 m^2^);Known to coagulation dysfunction (with typical clinical diagnosis or clear laboratory test results);Patients with mental illness or cognitive impairment, or severe depression;Patients who are not suitable to participate in this study or who are likely to withdraw from the study based on the judgment of the researchers; andPatients participating in other clinical trials.

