#### Randomization and blinding

A total of 340 participants will be randomly allocated into the treatment group or the control group. Each hospital will recruit 17 patients. In this trial, we will carry out block randomization in a 1:1 ratio according to the sequence generated using SAS software version 9.4 (SAS Institute Inc. Cary, NC). Random allocation will be performed after eligible participants consent in written form and complete baseline assessments. The central randomization system provided by the third party was used to generate the allocation sequence (http://zysj.clindacro.com/login.aspx), and the sub-center researchers (urologists) logged in the randomization system after screening the patients, input the account number and password, input the basic information of the subject according to the prompt, and the random system will give the subject code and random numbers. The sub-center therapists (acupuncturists) log into the central randomization system through their own account and password to check the subject codes, the random number, and treatment groups (acupuncture/non-meridian and non-acupoint shallow acupuncture). The participants, outcome assessors, and statisticians will be blinded to treatment allocation. The acupuncturist will not be blinded to the participant’s allocation. All participants in the study will sign a confidentiality commitment to avoid blind disclosure.

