**Fig. 1 Fig1:**
[figure not shown]
Trial flowchart. UI, urinary incontinence; PC, prostate cancer; PPI, prostatectomy incontinence

**Table 1 Tab1:** Study design schedule

Contents	Research period								
	Screening	Baseline	Treatment (W1–6)				Follow-up (W7–24)		
	W−1	W0	W1	W2	W4	W6	W12	W18	W24
**Visit**	V0	V1	V2	V3	V4	V5	V6	V7	V8
**Name**	×	×							
**Age**	×	×							
**Contact information**	×								
**Inclusion/exclusion criteria**	×								
**Informed consent**	×								
**Screening dispose**	×								
**Randomization**	×								
**Vital signs**^**1**^	×	×	×	×	×	×			
**Blood routine**^**2**^	×	×				×			
**Urine routine**^**3**^	×	×				×			
**Biochemical items**^**4**^	×	×				×			
**ECG**^**5**^	×	×				×			
**Height**		×							
**Weight**		×							
**BMI**^**6**^		×							
**Education and occupation**		×							
**Karnofsky score**		×							
**ECOG score**^**7**^		×							
**Personal history**^**8**^		×							
**Past histories**		×							
**Physical examination**^**9**^		×	×	×	×	×			
**Diagnosis time**		×							
**Pathological type**		×							
**Gleason score**		×							
**Clinical stages**		×							
**Operation type**		×							
**Treatment of PPI**		×	×	×	×	×	×	×	×
**Treatment of PCa**		×	×	×	×	×	×	×	×
**Daily water consumption**		×	×	×	×	×	×	×	×
**Drink preference**		×	×	×	×	×	×	×	×
**Postoperative extubation time**		×							
**Time of incontinence**		×							
**ICIQ-UI SF**^**10**^		×				×	×	×	×
**1-h pad test**		×			×	×			
**72-h voiding diary**		×	×	×	×	×	×	×	×
**EPIC-26**^**11**^		×				×	×	×	×
**SAS**^**12**^		×				×	×	×	×
**Weekly consumption of pads**		×	×	×	×	×	×	×	×
**Severity of PPI**		×				×	×	×	×
**Self-assessment**						×	×	×	×
**Blind assessment**						×			
**Major AE of PCa**^**13**^			×	×	×	×	×	×	×
**AE**^**14**^			×	×	×	×	×	×	×
**SAE**^**15**^			×	×	×	×	×	×	×

Notes:

^1^Vital signs: blood pressure, pulse, body temperature, and respiration

^2^Blood routine: hemoglobin, red blood cell count, white blood cell count, lymphocyte, neutrophil, and platelet count

^3^Urine routine: white blood cell, red blood cell, protein, and ketone body

^4^Biochemical items: alkaline phosphatase, alanine aminotransferase (ALT), aspartate aminotransferase (AST), total bilirubin, urea nitrogen, glomerular filtration rate, creatinine, glucose, triglyceride, total cholesterol, high-density lipoprotein, low-density lipoprotein, potassium, sodium, calcium

^5^ECG: electrocardiogram

^6^BMI: body mass index

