#### Statistical analysis

Summary tables (descriptive statistics and/or frequency tables) will be provided for all variables as appropriate. The primary outcome analysis will use the Cochran-Mantel-Haenszel (CMH) test. For continuous variables, means and standard deviations will be presented, unless the variable has a skewed distribution, in which medians, 25th and 75th percentiles will be presented. For other categorical data, between-group comparisons will be performed using a Wilcoxon rank-sum test, chi-square test, or Fisher’s exact test, as appropriate. AE incidences for each treatment group will be tested by the *χ*^2^ test or Fisher’s exact test as appropriate. All the statistical analysis will be performed using SAS version 9.4 (SAS Institute Inc) with 2-sided tests at a significance level of < 0.05. We will use the multiple imputation to handle missing data.

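### The plan admits men at any time after surgery and calls the condition self-limiting, but its stated primary analysis does not use time since surgery: a modest, cheaply recovered loss of precision

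*Protocol article*

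**What the plan says.** - **Natural course.** The Discussion states: "Although urinary incontinence after prostate cancer heals within half a year".
- **Entry.** The surgical inclusion criterion reads: "Patients who have received radical prostatectomy with a definite pathological diagnosis of prostate cancer". Neither eligibility list gives a minimum or maximum time since the operation. The only 6-month limit concerns another matter: "Currently receiving less than 6 months treatment similar to acupuncture".
- **Randomization.** Under Randomization and blinding: "we will carry out block randomization in a 1:1 ratio". No stratification factor is named.
- **Primary outcome and analysis.** The Abstract defines the outcome as the change in ICIQ-UI-SF "score at the week 6 from the baseline". The Statistical analysis section says: "The primary outcome analysis will use the Cochran-Mantel-Haenszel (CMH) test". It names no stratum or covariate.
- **Baseline data.** Table 1 has rows for "Time of incontinence" and "Postoperative extubation time". The Baseline assessment section includes operation history. Table 1 has no row for date of surgery or time since surgery.

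**The concern.** If the condition tends to resolve within about six months of surgery, time since surgery predicts how far a man's score will fall whatever his allocation. A man enrolled soon after the operation may improve a good deal over six weeks; a man enrolled years later probably will not. With open entry both kinds can be in the trial. The follow-up of 24 weeks is about as long as the recovery period that the authors describe, so the spread may matter more at the later visits.

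An analysis that leaves this variation in the error term estimates the treatment effect less precisely than it could. The authors name the recovery period themselves and already collect a related variable, so the gain is available at little cost.

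**Working it through.** **Inputs from the Sample size calculation section:** difference 2.5, common SD 6.3, two-sided alpha 0.05, power 90%, dropout 20%, 170 per arm.

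**1. Reproduce the stated sample size.**
- n per arm = 2 × 6.3² × (1.960 + 1.282)² / 2.5² = 133.5, so 134.
- Allowing for dropout: 134 / 0.8 = 167.5, so 168 per arm and 336 in total. The stated figure is about 340.
- Completers: 170 × 0.8 = 136 per arm. The standard error is 6.3 × √(2/136) = 0.764 and 2.5 / 0.764 = 3.27. Power is 90.5% by the normal approximation and 90.3% by the t distribution.

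The figure stands. It is an unadjusted comparison of two means with no term for time since surgery.

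**2. Variance that time since surgery could explain.** The document gives neither the share of early men nor their extra recovery. *Assumptions:* half the men are early, they recover g = 3 to 5 points more than the rest, and the planning SD of 6.3 already contains this variation.
- Variance due to the early/late split = 0.5 × 0.5 × g².
- g = 3: 2.25 / 6.3² = 2.25 / 39.69 = 5.7%.
- g = 5: 6.25 / 39.69 = 15.7%.

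**3. Power after adjustment.** Residual SD = 6.3 × √(1 − R²), with 136 per arm and t-based power.

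| R² | Basis | Residual SD | Power |
|---|---|---|---|
| 0 | as planned | 6.30 | 90.3% |
| 5.7% | half early, g = 3 | 6.12 | 91.9% |
| 10% | assumed | 5.98 | 93.0% |
| 15.7% | half early, g = 5 | 5.78 | 94.4% |

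The gain is about 2 to 4 percentage points. Any further gain from adjusting for baseline ICIQ-UI-SF is not counted.

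**4. Chance imbalance in early men.** With half early and 136 per arm, the 95% range of the between-arm difference in proportions is ±1.96 × √(2 × 0.25/136) = ±11.9 percentage points. Multiplied by 3 to 5 points, this gives ±0.36 to ±0.59 points. The 95% range of the whole unadjusted estimate is ±1.96 × 0.764 = ±1.50 points. The imbalance is one component of that range and does not add to it.

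**The case against.** **The analysis plan may already deal with this.** CMH is built to take strata, the article does not state them, and a condensed article commonly leaves them to an analysis plan, which is not shown here. This stands in part: it cannot be said that the trial will ignore time since surgery. What can be said is that the article fixes a method for the primary outcome and names nothing to go with it. Even a stratified CMH test would take a continuous time or baseline score only after grouping. The open entry does not depend on the unseen plan.

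**Nothing stated is invalid.** This stands. Recovery acts in both arms, and broad entry is a legitimate design choice. Three stronger readings are tempting and are not supported:
- *Natural recovery biases the result.* Randomization against sham prevents systematic bias. The shift of 0.36 to 0.59 points in step 4 is the edge of a 95% range under assumed inputs. It is already in the standard error and does not raise the type I error.
- *The trial is underpowered, or its effect is diluted by men who recover anyway.* The stated power reproduces. The document does not show that the SD of 6.3 leaves out recovery, and it gives no figure for a smaller effect in early men.
- *The needed variable is already in the database.* Table 1 has no surgery-date row. "Time of incontinence" is undefined and at best a proxy. "Postoperative extubation time" is also undefined and need not measure time since surgery.

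**The healing sentence is loose background.** This is fair. It does not quantify recovery, so the sizes above are scenarios, not estimates.

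**Conclusion.** The point holds as a matter of efficiency. The document says that recovery occurs within about half a year, admits men at any time after surgery, and states a primary analysis that names neither time since surgery nor its recorded proxy. The comparison remains valid and the 90% power is correct on the stated inputs.

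The size rests on three assumptions: half the men are early, they recover 3 to 5 points more, and this variation lies within the planning SD. On these, about 6% to 16% of the variance is recoverable and power rises from about 90% to 92–94%. A smaller share of early men or a smaller difference in recovery would give less. The change is worth making because it costs little, not because the trial depends on it.

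**What to change.** Before unblinding, pre-specify the following in the analysis plan, or confirm that it is already there:

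1. **Primary model.** A linear model (ANCOVA) for week-6 ICIQ-UI-SF, with treatment, baseline ICIQ-UI-SF and time since surgery as covariates. It estimates a difference in means, the quantity on which the sample size was based.
2. **Source of the variable.** Take time since surgery from the operation history. If no surgery date can be obtained, use "Time of incontinence", with its definition stated. Fix the choice in advance.
3. **If CMH is kept.** Use up to 6 months versus more than 6 months since surgery as a stratum.
4. **Other analyses.** Use the same variables in the week 12, 18 and 24 analyses of ICIQ-UI-SF and in the multiple imputation model.

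**Cost.** The first option replaces the stated primary test, so it needs a documented amendment and is more than a change of wording. Surgery dates may have to be retrieved from hospital records at 20 sites. Eligibility, randomization, treatment and sample size do not change.

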## Trial status

The trial was registered on www.Chictr.org.cn. ChiCTR2100042500. This trial is currently recruiting participants and will be completed by 31 December 2022.

Protocol completed date: 10 May 2021

Protocol amendment number: 03
